### **3. STUDY DESIGN**

- **Type/design of trial:** cross-over design
- **Primary outcome:**

Comparison of efficacy as measured bone -markers (serum CTx) between generic and brand alendronate formulations

With regard to the primary outcome we hypothesise that there is no difference between brand versus generic alendronate
- **Secondary outcome:**

Comparison of tolerability between brand and generic alendronate formulations
- **Study population and sample size:**

30 postmenopausal women with a prior fracture and osteoporosis, as diagnosed by DEXA (dual X-ray energy), with or without a previous fracture
- **Study location:**

out -patient, single-centre, VieCuri MC voor Noord-Limburg
- **Duration of screening period and follow-up:**

The screening period will be a maximum of 2 weeks

Intervention period: 24 weeks; i.e. 2 times (before and after cross-over) 12 weeks
- **Description of intervention and administration:**

After randomization, single blinded, open label administration of alendronate

15 patients start with generic alendronate and 15 patients with brand oral alendronate once weekly

After the first period of 12 weeks, cross-over to branded and generic oral alendronate once weekly respectively

Evaluation of side-effects, adherence and medication use (by questionnaires) and efficacy (by bone-markers) at day 1, week 4, 12, 16 and 24

After the study period of 24 weeks patients will continue treatment with the alendronate formulation they prefer, according to current practice.

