## **9. STATISTICAL CONSIDERATIONS**

The hypothesis tested in this trial is a non-inferiority in efficacy based on the outcome parameter: serum CTx resorption bone marker at visit 3 and 5 (week 12 and week 24) of both treatment groups.

De CTx outcome will be expressed in standardized Z-scores. Z-scores can be used to compare a measurement to a reference value. The Z-score is the number of standard deviations away from the average value of the age and gender specific reference group (i.e. women of the same age). A difference < 0.5SD (in terms of serum Ctx Z-scores) between brand and generic alendronate is considered not to be clinically relevant.

Sample size is calculated ( $N = (Z_{\alpha} + Z_{\beta})^2 \cdot Sd^2 / d^2$ ; paired observations) based on  $\alpha = 0.05$  (95% confidence interval),  $\beta = 0.1$  (power 90%), with a standard deviation of sCTx measurements of 0.5 SD (S) and d as the difference between the mean of both treatment groups. Considering a serum CTx Z-score difference of < 0.5 SD between both groups as not clinically relevant, a sample size of 30 patients is needed to test the non-inferiority hypothesis.

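### The stated sample size of 30 does not follow from the formula and inputs printed beside it, which give 9 or 11 patients (18 or 22 if the SD is that of a single measurement)

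*Protocol*

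**What the plan says.** Protocol Section 9 (Statistical Considerations) sets a non-inferiority hypothesis on serum CTx at weeks 12 and 24. It gives the sample-size formula N = (Z_alpha + Z_beta)^2 × Sd^2 / d^2 and labels it for "paired observations". The inputs are alpha 0.05, glossed as a "95% confidence interval", and power 90%. The variability and the difference enter as follows: "with a standard deviation of sCTx measurements of 0.5 SD (S) and d as the difference between the mean of both treatment groups". No separate number is given for d. The only candidate is the margin: "Considering a serum CTx Z-score difference of < 0.5 SD between both groups as not clinically relevant". The paragraph ends by saying that "a sample size of 30 patients is needed to test the non-inferiority hypothesis".

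The Précis repeats 30, and Section 3 splits it by sequence: "15 patients start with generic alendronate and 15 patients with brand oral alendronate once weekly". Section 9 states no dropout allowance, no within-patient correlation and no source for the SD. Section 7.2 says that removed subjects are not replaced.

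**The concern.** The protocol prints the formula, the inputs and the answer in one paragraph, so a reader can check it directly, and the answer is about three times what the inputs yield. A later analysis plan could not repair this, because the protocol itself makes the calculation.

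Two further features make the paragraph hard to trace. The formula calls for the SD of the within-patient difference between treatments, whereas the text supplies the SD of the measurements. It also describes d as a difference between the means of two groups, although the observations are paired. At stake is whether the 90% power claim and the claim that 30 patients are required can be relied on, and what power the trial really has.

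**Working it through.** **Inputs, all from Protocol Section 9.** SD = 0.5; d = 0.5 (the margin, as the only figure offered); power 90%, so Z_beta = 1.282; alpha = 0.05 with sidedness not stated. Two values of Z_alpha are therefore tried: 1.645 (one-sided 5%) and 1.960 (95% confidence interval, equal to one-sided 0.025).

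**1. The plan's own figure, with SD and d as printed.** Sd^2 / d^2 = 0.25 / 0.25 = 1, so N = (Z_alpha + Z_beta)^2.

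- One-sided 5%: (1.645 + 1.282)^2 = 8.56, so 9.
- 95% CI: (1.960 + 1.282)^2 = 10.51, so 11.

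Using the t distribution instead of the normal gives 11 and 13. The stated 30 is not reproduced.

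**2. 0.5 read as the SD of a single measurement.** Then Sd^2 = 2 × 0.25 × (1 − rho), where rho is the within-patient correlation. With rho = 0, Sd = 0.5 × √2 = 0.707.

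- One-sided 5%: 2 × 8.56 = 17.1, so 18.
- 95% CI: 2 × 10.51 = 21.0, so 22.

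The t distribution gives 19 and 24. Any positive correlation lowers these numbers.

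**3. Two-group formula.** This gives 18 or 22 per group, 36 or 44 in total. It does not give 30 either, and it is not the paired formula that is printed.

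**4. What would give 30.** None of these routes is stated in the protocol.

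| Route to 30 | Value needed |
|---|---|
| Larger SD of the difference, d = 0.5 | Sd = 0.5 × √30 / 3.242 = 0.845 (95% CI), or 0.936 (one-sided 5%) |
| Smaller d, Sd = 0.5 | d = 0.5 × 3.242 / √30 = 0.296 (95% CI), or 0.267 (one-sided 5%) |
| Dropout allowance starting from 22 | 1 − 22/30 = 27% |
| Dropout allowance starting from 11 or 9 | 63% or 70% |

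The closest combination of standard adjustments stacks √2 on the SD, two-sided alpha, beta/2 as in an equivalence test, and a t correction. It gives 28, but Section 9 mentions neither the √2 nor the beta/2 step.

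**5. Actual power of 30 patients.** This uses a margin of 0.5, a true difference of zero, a paired t test at one-sided 0.025 (the 95% CI reading) and the noncentral t distribution.

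| Sd of the paired difference | Power at N = 30 |
|---|---|
| 0.5 (as printed) | above 99.9% |
| 0.707 (0.5 is a single-measurement SD, rho = 0) | 96% |
| 0.845 (assumed) | 88% |
| 1.0 (assumed) | 75% |

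The last two rows are a sensitivity range; the protocol states neither SD. The third row falls just short of 90% because the SD of 0.845 was solved with the normal approximation and the power uses t.

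**The case against.** The strongest reply is that the discrepancy is conservative. On both paired readings of the stated SD, 30 patients exceed the requirement, with power above 99.9% or about 96%. Nothing stated in the protocol leads to a power below 90% in the paired analysis. The lower figures need an SD of the paired difference of 0.845 or 1.0, which the protocol does not give. An allowance for loss may also have been added without being written down: 22 / 0.73 is about 30, and removed subjects are not replaced. This reply stands as far as it goes. It shows that the trial is not demonstrably too small, but it does not make the printed calculation correct.

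A reader might go further and infer that the sample size was computed for a margin of about 0.30, since Sd = 0.5 and d = 0.30 give 29.2, rounded up to 30. The trial would then be judged against a margin wider than the one it was sized for. The protocol does not support this. It nowhere mentions 0.30, and Section 9 gives 0.5 SD twice and consistently as the threshold of relevance. The match holds only with Z_alpha = 1.960; one-sided 5% gives 23.8, so 24. A larger SD or an unstated allowance reaches 30 equally well. A back-solved value is no evidence of the intended margin and no reason to change one set on clinical grounds.

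Nor is 0.5 shown to be wrong because a Z-score has SD 1 in its reference group. That SD belongs to the reference population; it fixes neither the spread among treated women with osteoporosis nor the SD of their within-patient differences. Asking for a source is fair. Finally, 15 patients per sequence add up to 30, so Section 3 is consistent with Section 9 and is not itself an error.

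**Conclusion.** The point holds as an error in the stated calculation. With the formula and inputs in Section 9, N is 9 (one-sided 5%) or 11 (95% CI), and 18 or 22 if 0.5 is the SD of one measurement and the paired values are uncorrelated. So the claims that 30 are needed, that power is 90%, that the SD is 0.5 and that d is 0.5 cannot all be true without a step the text omits. At least one of the size, SD, d, power or an unstated dropout allowance is misreported, and the protocol does not show which.

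Neither a loss of power nor an invalid decision rule has been shown. The conclusion rests on taking d as the 0.5 margin, the only figure offered, and on a true difference of zero. The real power of 30 depends on the SD of the paired difference, which the protocol does not give.

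**What to change.** Rewrite the sample-size paragraph in Section 9. Keep the stated 0.5 margin and the 30 patients. State:

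- whether alpha is one-sided 5% or the one-sided 0.025 that a 95% confidence interval implies;
- the SD of the within-patient difference in serum CTx Z-score, with its source (if only a single-measurement SD is known, give the assumed within-patient correlation);
- the value of d used, described as a mean within-patient difference;
- any dropout allowance.

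Replace the claim that 30 are needed with the number that follows. On the 95% CI reading this is 11, or 22 if 0.5 is the single-measurement SD with uncorrelated pairs; on one-sided 5% it is 9 or 18. Then give the actual power of 30 at the SD adopted, with the range in the power table above as sensitivity. If an allowance for loss explains the gap, say so and show it.

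The cost is one paragraph, with no extra patients and no change to design, margin or visits. It should be settled before outcome data are seen.

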## **10. PARTICIPANT RIGHTS AND CONFIDENTIALITY**

### **10.1 Institutional Review Board (IRB) Review**

This protocol and the informed consent document - Appendix 4 - and any subsequent modifications will be reviewed and approved by the ethics committee responsible for oversight of the study.

### **10.2 Informed Consent Form**

See appendix 4

## **11. ETHICAL CONSIDERATIONS**

All subjects participating in this study will be informed in writing and verbally about the purpose and procedures of the study by the investigator or research coordinator. All subjects will be provided an informed consent form describing this study and providing sufficient information for subjects to make an informed decision about their participation in this study. (See Appendix 4: Subject Informed Consent Form). This consent form will be submitted with the protocol for review and approval by the Ethical Committee aZM/UM.

The formal consent of a subject (by signing the approved consent form) must be obtained before that subject undergoes any study procedure. The consent form must be signed and dated by both the subject and the investigator. The subject will be provided with a signed copy of the informed consent.

Subjects' confidentiality will be ensured by the investigator and will be maintained by the following procedures:

- Subjects will be coded by their initials and a specific study number. This code will be used on all study forms or other documents with regard to this study.

The individual participants number is based on the year and month at entrance of the study, with the adaptation of number 1 to 30. For example: 091201 (start of participation in study in December 2009, 1st participant) or 100125 (start January 2010, 25th participant)

- Documents that are needed in compliance with Federal regulations/ICH GCP guidelines e.g. signed informed consents, subjects identification list, will be kept at a secure location and in strict confidence by the investigator.

Subjects are free at all time to discontinue participating in the study, without providing any reason for discontinuation.

An independent physician is available for questions of the subjects.

Subjects will be informed about the outcome of the trial.

All data collected will be kept for 15 years after completion of the study.

Participating subjects will be insured by Medirisk VieCuri MC voor Noord-Limburg

## **12. PUBLICATION OF RESEARCH FINDINGS**

The CCMO statement on publication policy will be followed ([www.ccmo.nl](http://www.ccmo.nl)). See appendix 6.

Both positive and negative results of this trial will be disclosed unreservedly and will be submitted for publication in a peer-reviewed scientific journal. None of the parties concerned has a right of veto and disputes on the interpretation of the results may not lead to unnecessary

delay in publication. For detailed information we refer to the CCMO statement on publication policy.

## APPENDICES

- Appendix 1: GSRS
- Appendix 2: SEAMS
- Appendix 3: BMQ
- Appendix 4: Informed consent
- Appendix 5: SAE form
- Appendix 6: CCMO statement on publication policy
- Appendix 7: Informatie proefpersonen verzekering, versie augustus 2008
- Appendix 8: SUSAR meldformulier, versie juni 2006
- Appendix 9: Voortgangsrapportage formulier, versie september 2009
- Appendix 10: Formulier melding (voortijdige) beëindiging studie, versie augustus 2009
- Appendix 11: Contract Procter and Gamble
